#### Secondary outcomes

In addition to the four principal outcomes, the MAAUI study has a number of prospectively-defined secondary outcomes:

• The study will re-evaluate the primary outcomes in the following two physician subgroups: physicians who received the audit and feedback material and attended the CME workshop; physicians who received the audit and feedback material and chose not to attend the CME workshop. This analysis will help to determine the impact that the different components of the educational intervention had on physician behaviour.

Specifically in the subgroup of physicians who attended the CME workshop:

• The study will measure the change in physician knowledge of osteoarthritis from pre-CME workshop to immediately post-CME workshop and the change in knowledge from pre-CME workshop to five months post-CME workshop. These two outcomes should provide insight into physicians' retention of information following a CME workshop and will allow us to examine any relationship between change in physician knowledge and change in physician prescribing behaviour.

• The study will also survey physicians' perceived change in prescribing behaviour at five months post-intervention. This outcome, compared with the principal study outcomes, will provide insight into the accuracy with which physicians' discern their own prescribing practices.

• The study will collect process-related measures in order to mark areas for improvement in the study interventions. Specifically, physicians' impressions of the Personalised Prescribing Profile and CME workshop will be surveyed using the questionnaire distributed immediately following the CME workshop and using focus-group discussions at the end of the study follow-up. All workshop participants will be invited to attend a follow-up focus group (one for urban participants and one for rural participants). A separate focus group will be held for the workshop facilitators.

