In this paper, we describe a randomized controlled study, which we are presently conducting, to evaluate the impact of an educational intervention on primary care physicians' prescribing of non-steroidal anti-inflammatory therapies. The study, being conducted in the province of Manitoba, Canada, tests the hypothesis that this intervention will significantly improve physician appropriate prescribing of anti-inflammatory drugs in compliance with international clinical practice guidelines and Manitoba's restricted drug reimbursement policy [18-22]. The intervention being tested is modelled on proven approaches to changing physician behaviour; it consists of an audit and feedback mechanism with optional participation in a Continuing Medical Education (CME) interactive workshop. This manuscript summarizes Phases II to V of a larger initiative entitled the Manitoba Appropriate Anti-Inflammatory Utilization Initiative (MAAUI). The study began in November 2000 and is currently in the data analysis stage. In this paper, we relate in detail the protocol of this randomized controlled study.

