### Study design

The MAAUI study design is depicted in Figure 1. Primary care physicians were allocated to the control and intervention arms of the study using a stratified randomization process. Specifically, study participants were divided into groups according to the geographical area of their practice within Manitoba. These groups were stratified by physicians' "urban" (within Winnipeg – the provincial capital, population size 676,700) or "rural" (outside of Winnipeg, population size 468,300) practice location. Randomization within each stratum was then carried out at the level of the group. The MAAUI research team originally identified 12 urban and 11 rural areas in Manitoba based on existing community boundaries within Winnipeg and the presence of distinct regional health districts outside of Winnipeg. Because one urban and rural area each contained very few primary care physicians (less than five), these areas were joined to neighbouring regions resulting in 11 urban and 10 rural groups. Urban and rural groups were randomized in such a way as to achieve a 1:2 ratio of control to intervention groups. Four of the urban groups and three of the rural groups were randomized to the control arm, and the remaining seven urban and seven rural groups were randomized to the intervention arm.

This study design was chosen for several reasons. First, it offered the scientific rigour that is associated with randomization and the use of a control group. It also ensured that both rural and urban Manitoban physician groups had an equal opportunity to take part in and learn from the study intervention. The study design was also particularly amenable to testing an intervention that required physicians to congregate in common locations (i.e. for the CME workshop). The 1:2 ratio of study groups helped to ensure that there were a sufficient number of study participants who would consider attending the CME workshops.

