### The educational intervention

Physicians allocated to the intervention arm of MAAUI were mailed a package that included an introduction to the study, audit and feedback material, and an invitation to participate in a CME workshop. Physicians in the control arm received no package.

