#### CME workshop

The CME workshop for MAAUI was entitled "The Utilization and Prescribing of Anti-inflammatory Drugs in Osteoarthritis". The workshop focused specifically on the prescribing for osteoarthritis, as it was felt that people with this disease account for a large proportion of the chronic non-steroidal anti-inflammatory use by primary care practices [39].

Eleven CME workshops were held throughout Manitoba (four within Winnipeg and seven outside of Winnipeg) and physicians in the intervention group were invited to voluntarily attend one of the 11. The workshops were free of charge and were approved for 3.0 hours of MAINPRO-M1 credits (continuing education credits awarded by the College of Family Physicians of Canada for group learning activities). Each workshop was facilitated by a trained family physician.

The workshops included three components: an introductory video, a decision tree, and a case study portion. The introductory video provided the history and rationale of MAAUI, explained aspects of the Personalised Prescribing Profile, and introduced the decision tree. The decision tree depicted a stepwise approach to the diagnosis and treatment of osteoarthritis. This aid was designed by a rheumatologist on the MAAUI research team specifically for use in the study and was based on international clinical practice guidelines and Manitoba's drug reimbursement policy [18-22]. A take-home copy of the decision tree was provided to each workshop participant (see Additional file 1). Finally, the case study portion of the workshop consisted of studies exploring both the diagnosis and appropriate treatment of osteoarthritis. These case studies were supplied from an existing CME curriculum entitled "Clinical Scenarios in Osteoarthritis" [40].

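### The attender and non-attender re-analysis is meant to inform on component impact, but attendance was voluntary and no contrast using these subgroups is randomised

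*Protocol article*

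**What the plan says.** The Background section of the protocol article describes a single intervention: "it consists of an audit and feedback mechanism with optional participation in a Continuing Medical Education (CME) interactive workshop". Under Study design, allocation is by geographical area: "Randomization within each stratum was then carried out at the level of the group". There are two arms only, with four urban and three rural areas as controls, while "the remaining seven urban and seven rural groups were randomized to the intervention arm". Under The educational intervention, the profile and the workshop invitation go out in one mailing, and "Physicians in the control arm received no package". Under CME workshop, "physicians in the intervention group were invited to voluntarily attend one of the 11".

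The first item under Secondary outcomes re-evaluates the four principal outcomes in two subgroups of the intervention arm. One is the physicians who attended. The other is "physicians who received the audit and feedback material and chose not to attend the CME workshop". The stated purpose follows: "This analysis will help to determine the impact that the different components of the educational intervention had on physician behaviour".

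Baseline data collection lists sex, urban or rural location, years in practice, prescribing volume and baseline rate of appropriate prescribing. Sample size and statistics enters these baseline data as control measures in the regression for the primary outcomes. It does not say whether the same model is used for the subgroups.

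**The concern.** The two subgroups are formed by the physicians themselves after randomisation. Physicians who give up time for a voluntary workshop may be the ones already inclined to change their prescribing. A difference between attenders and non-attenders, or between either subgroup and the controls, may then reflect who chose to attend as well as what the workshop or the profile did.

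The two components are also hard to separate for a second reason. The invitation arrived with the personal profile, so the decision to attend may itself be a response to the feedback.

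What is at stake is the attribution of any benefit to one component or the other. The design considerations in the protocol include affordability, practicality and reproducibility, so it matters to anyone wishing to adopt the intervention whether the workshop is needed. An attribution distorted by selection could mislead on that point.

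**Working it through.** **No figure of the plan to reproduce.** The protocol gives no expected attendance, no subgroup size and no subgroup effect. Its minimum of 116 physicians per group belongs to the primary comparison and does not decide this point.

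**Which contrasts are randomised?**
- Package versus no package: yes, by area within urban and rural strata.
- Attenders versus non-attenders: no. Both are in the intervention arm and are separated by choice.
- Attenders versus controls: no. Controls are a mixture of would-be attenders and would-be non-attenders. They were never invited, so the two types cannot be told apart.
- Non-attenders versus controls: no, for the same reason.

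**Size of the bias.** Let m be the mean change, without any intervention, of physicians who would not attend, and m + g that of physicians who would. Here g is what remains after any covariate adjustment. Let a be the fraction who attend. Randomisation makes the expected share of would-be attenders among controls a as well. Setting both component effects to zero:
- control mean = a(m + g) + (1-a)m = m + ag
- attenders minus non-attenders = (m + g) - m = g
- attenders minus controls = (m + g) - (m + ag) = g(1-a)
- non-attenders minus controls = m - (m + ag) = -ag

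**Illustrative values.** Both g and a are assumptions. Biases are in percentage points of the appropriate-prescribing rate.

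| g | a | Attenders vs non-attenders | Attenders vs controls | Non-attenders vs controls |
|---|---|---|---|---|
| 1 | 25% | 1 | 1 × 0.75 = 0.75 | -0.25 × 1 = -0.25 |
| 5 | 25% | 5 | 5 × 0.75 = 3.75 | -0.25 × 5 = -1.25 |
| 5 | 50% | 5 | 5 × 0.50 = 2.50 | -0.50 × 5 = -2.50 |
| -5 | 25% | -5 | -5 × 0.75 = -3.75 | -0.25 × (-5) = 1.25 |

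The last row shows that a negative g reverses every sign.

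**Check on the primary comparison.** Weighting the two subgroup biases by their shares gives a·g(1-a) + (1-a)(-ag) = 0. With g = 5 and a = 25%, this is 0.25 × 3.75 - 0.75 × 1.25 = 0.9375 - 0.9375 = 0. The biases cancel when the arm is analysed whole.

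**Second illustration, by simulation.** Both component effects were set to zero. Assumed values were attendance of 20% to 50%, a correlation of 0.5 between motivation and the latent tendency to attend, and a correlation of 0.1 to 0.4 between motivation and change. Attenders then exceeded non-attenders by about 0.08 to 0.35 SD. Attenders looked 0.04 to 0.28 SD better than controls, and non-attenders 0.02 to 0.16 SD worse. These inputs are not in the document either, so the simulation shows a mechanism and a possible scale, not an estimate.

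**What adjustment can reach.** If the regression is carried over, it addresses sex, location, years in practice, volume and baseline rate. No listed covariate measures interest in the topic or readiness to change, so g need not be zero after adjustment.

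**The case against.** The case on the other side has several sound parts.

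- **Wording.** The protocol says only that the analysis will help towards an answer. It names no head-to-head contrast, and it is open throughout that attendance was optional. A reader might infer that the plan claims to show what each component achieved. The text does not go that far.
- **Existing adjustment.** The subgroup item re-evaluates the primary outcomes, so the natural reading is that the same covariate-adjusted model applies. Location and baseline prescribing would then be handled. The outcome is also a within-physician change, which removes stable differences in level. It would be wrong to treat these as uncontrolled confounders.
- **Magnitude.** A reader might infer from g = 5 that the bias is a third to a half of the 10% target. That ratio follows from the choice of g, and it reads 10% as percentage points, which the protocol does not state. Nor does the protocol support a positive g, so it cannot be said that the workshop must be flattered and the feedback understated.
- **Importance.** This is one secondary analysis, and the protocol mentions no payer decision that rests on it.
- **Condensed article.** The detail of a subgroup model may sit in a full protocol or analysis plan, and its absence here is no fault.

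These points limit the concern but do not remove it. The purpose given to the analysis is causal and is stated in the text, so it is not an omitted detail. Learning about components from these subgroups requires some contrast, and every available one is exposed to selection. Adjustment leaves unmeasured motivation, and a change score does not help when motivation is related to change itself.

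**Conclusion.** The concern holds in a limited form. Analysed as described, the two subgroups cannot supply a randomised estimate of the effect of either component, and nothing in the protocol says so. The bias is g, g(1-a) and -ag for the three contrasts. This rests on g being the difference in change between would-be attenders and others that remains after adjustment, and on the share of would-be attenders being the same in both arms in expectation. Because the document gives neither g nor a, the size and the direction are unknown, and the bias is zero if g is zero.

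A reader might infer that the trial's main conclusion is in doubt. It is not: the comparison of the whole package with control is by allocated arm and is not touched by this point. The point is worth correcting because it concerns a stated causal purpose and the correction is cheap.

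**What to change.** 1. State that only the effect of the combined package is randomised.
2. Replace the component-impact sentence under Secondary outcomes with one such as: results in attenders and non-attenders are exploratory and non-randomised, and do not by themselves separate the effect of the workshop from that of the feedback.
3. Compare each subgroup with control physicians using the baseline covariates already collected, and keep the clustering by area. Either regression will do, or weighting of controls by an attendance probability modelled in the intervention arm.
4. State that either method assumes attendance is ignorable given those covariates. Weighting balances only what was measured, so it does not remove unmeasured motivation.

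Once attendance is known, a can be put into the formulas above to report how large g would have to be to account for each subgroup result.

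The cost is a change of wording and modest extra analysis. No new data are needed. The price is a weaker secondary claim.

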### Baseline data collection

The following data were collected at baseline (October 1^st^, 2000 to July 31^st^, 2001) as control measurements: i) physician demographics including sex, urban or rural practice location, and the number of years in practice; ii) physician volume of non-steroidal anti-inflammatory therapies prescribed annually for patients requiring chronic therapy; and iii) physician rate of appropriate prescribing of NSAIDs. These latter two measures were assessed for each of coxibs, traditional NSAID/GPA combination therapy, and traditional NSAID monotherapy.

### Sample size and statistics

Sample size was calculated based on the need to detect at least a 10% improvement in physician practice patterns associated with the intervention, for clinical significance. Alpha error was set at 1% because of the multiple primary outcomes and power was set at 80%. It was also assumed in the sample size calculation that physician baseline demographic measures and baseline practice patterns would contribute an additional 10% variation to the outcomes. Based on these figures and using sample size techniques for multivariate regression analysis [44], we estimated the need for a minimum of 116 physicians in the control group and intervention group respectively.

Multivariate regression analysis will be used to determine if the study intervention has a significant impact on the primary outcomes. Baseline data will be included as control measures and interaction effects between these baseline data and the intervention will also be evaluated.

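### The minimum of 116 physicians per arm for 80% power makes no allowance for randomising 7 control and 14 intervention areas

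*Protocol article*

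**What the plan says.** In Methods, Sample size and statistics, the aim is the "need to detect at least a 10% improvement in physician practice patterns associated with the intervention". The error rates follow: "Alpha error was set at 1% because of the multiple primary outcomes and power was set at 80" (per cent). Baseline measures are assumed to account for a further share of variation; they "would contribute an additional 10% variation to the outcomes". From these figures, "using sample size techniques for multivariate regression analysis", the article concludes that "we estimated the need for a minimum of 116 physicians in the control group and intervention group respectively".

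In Methods, Study design, the unit of allocation is the area: "Randomization within each stratum was then carried out at the level of the group". "Four of the urban groups and three of the rural groups were randomized to the control arm", which makes 7 control areas; the other 7 urban and 7 rural areas make 14 intervention areas.

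Two other places bear on the number analysed. Study population gives about 884 eligible physicians, all entered automatically, with an option to withdraw in the intervention arm. Principal outcomes withholds the data of any physician with fewer than five long-term patients in either period.

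**The concern.** The article lists the inputs and says that 116 follows from them. An ICC, a design effect and the number of areas are not among them. A regression sample-size method with those inputs treats each physician as independently allocated. Physicians in one area share an allocation and may share prescribing habits, so 116 physicians in 7 areas carry less information than 116 independent ones. In addition, the arm comparison rests on only 21 randomised units.

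What is at stake is how the results will be read. The figure of 116 per arm is the only adequacy benchmark in the document. A null result on one of the four principal outcomes, with somewhat more than 116 physicians analysed in each arm, could be taken as adequately powered when it was not.

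**Working it through.** **Can 116 be reproduced?** Not uniquely. The article gives no SD, no number of predictors and no sidedness, and does not say whether the 10% is percentage points, a relative change or a share of variance. Two routes reach 116:

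- Two means, per arm, two-sided 1%, 80% power. (2.576 + 0.842)² = 11.68, so n = 2 × 11.68 / d² = 116 gives d = √(23.36/116) = 0.449. If the effect is 10 points, the SD is 10/0.449 = 22.3 points.
- A share of variance, as a total N. 11.68 / (0.10/0.90) + 10 + 1 = 116.1 with 10 predictors, or 11.68/0.10 = 116.8. Here 116 is the total and not the number per arm.

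Both routes treat physicians as independent. The main calculation uses the first, because the article says 116 in each group.

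**Cluster power.** Inputs: 7 and 14 areas (Study design); d = 0.449 (back-solved above); two-sided alpha 0.01; areas of equal size within each arm (assumption); ICC 0.02, 0.05 and 0.10 (assumptions, since none is stated).

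- Design effect in each arm: DE = 1 + (m − 1) × ICC, where m is physicians per area.
- Variance of the difference in SD units: V = DE₀/n₀ + DE₁/n₁.
- Power from a noncentral t with noncentrality d/√V. Degrees of freedom are 21 − 3 = 18 (21 areas, less intercept, arm and urban/rural stratum); the critical value is 2.878.

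Worked case, 116 v 116 at ICC 0.05:

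- m is 116/7 = 16.6 and 116/14 = 8.3.
- DE₀ = 1 + 15.6 × 0.05 = 1.78 and DE₁ = 1 + 7.3 × 0.05 = 1.36.
- V = 1.78/116 + 1.36/116 = 0.0271 and √V = 0.165.
- Noncentrality = 0.449/0.165 = 2.73, so power is 46%.

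| Physicians analysed (control v intervention) | ICC 0 | ICC 0.02 | ICC 0.05 | ICC 0.10 |
|---|---|---|---|---|
| 116 v 116 | 70% | 59% | 46% | 33% |
| 116 v 232 (1:2) | 84% | 71% | 54% | 37% |
| 147 v 295 (half of 884) | 93% | 80% | 61% | 40% |
| 295 v 589 (all 884) | 99.9% | 95% | 75% | 48% |

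Part of the loss at 116 v 116 comes from the 18 degrees of freedom: power is already 70% at ICC 0. A normal approximation removes that part and returns 80% at ICC 0, but still gives 69%, 56% and 40% at the three positive ICCs.

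With all 884, power is 82% at ICC 0.04 and falls through 80% just above 0.043.

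The number of areas sets a ceiling. With unlimited physicians, V tends to ICC × (1/7 + 1/14). At ICC 0.10 this is 0.0214, so the noncentrality is 0.449/0.146 = 3.07 and power cannot exceed about 58%.

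**Sensitivity to the derivation.** If 116 was really a total, d is about 0.63 (58 per arm) to 0.67 (10% of variance in equal arms). Then 116 v 116 gives about 92–94%, 82–86% and 66–72% at ICC 0.02, 0.05 and 0.10. With all 884 it gives at least 98% up to ICC 0.05, and 84–88% at 0.10.

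**The case against.** The strongest reply is that 116 did not set the size of the trial. It is called an estimated minimum, and every eligible physician was entered, about 884 in all. With most of them analysed, power is good at small ICCs. This stands. A reader might infer that the trial as a whole is underpowered; the documents do not support that, because the ICC and the analysed numbers are both unknown. Nor do they present 116 as a guarantee.

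A second reply is that the percentages rest on a back-solved effect. This also stands: on the total-N reading, 116 per arm keeps more than 80% at ICC 0.05. That reading does not rescue the text, however. It would mean that the article reports a total as a per-arm figure, which would itself need correcting, and the calculation would still contain no clustering term.

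Three further inferences should be resisted.

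- An equal minimum per arm does not conflict with 1:2 allocation. The control arm has to reach it and the intervention arm exceeds it.
- The article gives no counts, so it cannot be said that few physicians pass the five-patient rule, overall or for any drug class.
- The August 1999 to September 2000 profile data would not directly supply the right ICC. They cover one period, whereas the outcome is a pre-to-post change adjusted for baseline. Stable differences between areas cancel in a change score, so the relevant ICC could be quite different.

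**Conclusion.** The point holds in a limited form. The stated number and power belong to a design with independently allocated physicians, not to the 7 v 14 area design in the same article. Taking 116 per arm as exactly 80% (d about 0.45, two-sided 1%), power for 116 v 116 is below 80% at any positive ICC, at 33% to 59% over ICC 0.02 to 0.10. For 116 v 232 it is 37% to 71% over the same range.

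The omission of clustering from the listed inputs is certain. The size of the loss is not: it depends on an assumed ICC, equal area sizes and a derivation of 116 that cannot be confirmed. The conclusion concerns 116 as a benchmark and not the adequacy of the full study population. Whether the regression itself accounts for area is a separate question from this power statement.

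**What to change.** Withdraw 116 per arm as the measure of adequacy. In its place:

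1. Say what the 10% means (points, relative change or share of variance), and state the SD of the change and the sidedness of alpha.
2. Restate power, or the minimum detectable difference, for 7 control and 14 intervention areas. Use the physicians actually analysable for each of the four principal outcomes after withdrawals and the five-patient rule, with degrees of freedom based on the number of areas.
3. Give the result over an ICC range such as 0.01 to 0.10, preferably centred on the ICC of the baseline-adjusted change. If only the single-period ICC of the prescribing rate is available, say so and treat it as a rough guide.

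No extra enrolment is needed and the trial's conduct does not change. The cost is one recalculation and a less favourable power figure.
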